**Figure 1 fig1:**
[figure not shown]
Sample size flow chart.

### Procedure for the sLiFE program intervention

3.6

The intervention will take place in four different stages.

#### Stage one

3.6.1

Physiotherapists (who led the sessions) will establish the guidelines to be followed and the intervention dynamics (sessions will be carried out in the same way and with the same contents in all health centres). The manuals for professionals, in Spanish, will be used to guarantee the reproducibility (26).

#### Stage two

3.6.2

The intervention group (12–14 participants) will be given a brief guide in Spanish from the participant’s manual to advise them in carrying out the activities. The intervention group (*n* = 325) will do the balance activities (tandem stance, tandem walk, one-legged stand, leaning from side to side, leaning forward and backward, stepping over obstacles forwards and backwards, stepping over obstacles sideways) and strength activities (knee bends, sitting down and getting up from normal and low chairs, toe stand, toe walk, heel stand, heel walk, walking sideways, climbing stairs, and tightening muscles), the principles and implementation strategies (26). A total of five one-hour in-person sessions and two follow-up telephone sessions will be held.

#### Stage three

3.6.3

Implementation of the sLiFE program (26). The total intervention comprises twelve weeks according to the following schedule (Table 1).

**Table 1 tab1:** Session schedule.

Session/week	Balance	Strength
1 (on-site)/Week 1	*Tandem stance *Tandem walk	*Knee bends *Sitting down and getting up (normal chair/low chair)
2 (on-site)/Week 2	*Standing on one leg	*Toe stand *Toe walk *Heel stand *Heel walk
3 (on-site)/Week 3	*Leaning side-to-side *Leaning forwards and backwards	*Walking sideways *Climbing stairs
4 (on-site)/Week 4	*Stepping over obstacles forwards and backwards *Stepping over obstacles sideways	*Flexing muscles
5 (on-site)/Week 6	Rest	Rest
6 (telephone)/Week 8	Follow-up	Follow-up
7 (telephone)/Week 12	Follow-up	Follow-up

#### Stage four

3.6.4

Follow-up evaluation at six months.

Spirit figure has been added as Supplementary material.

### Variables

3.7

#### Sociodemographic variables

3.7.1

Participants’ age, education level, marital status, and profession will be noted. The prescribed pharmacological treatment, lifestyle habits, smoking history and smoking pattern and alcohol consumption will be collected.

#### Anthropometric variables

3.7.2

Height will be measured with the portable Seca 222 system, with the subject standing. The average of two measurements, rounded to the nearest centimetre, will be recorded. Weight will be measured using a SOEHNLE 7830 digital column scale.

Waist and hip circumference will be measured twice, the recommendations of the Spanish Society for the Study of Obesity will be followed.

Systolic and diastolic blood pressure will be measured with a validated OMRON M10-IT blood pressure monitor (Omron Health Care, Kyoto, Japan), the recommendations of the European Society of Hypertension will be followed.

#### Charlson Comorbidity Index

3.7.3

The Charlson Comorbidity Index (CCI) was developed in 1987 by Mary E. Charlson. It has been considered the gold-standard tool in clinical research as a prognostic index to predict mortality. This index is a standardized score calculated as a simple weighted sum of comorbidity item scores (27, 28). The original version of the CCI was composed on 19 items which correspond to different clinical comorbidities (27).

#### Frailty

3.7.4

Frailty will be measured following the five criteria of Fried’s phenotype (29): (1) Low muscle strength; (2) Poor nutrition; (3) Poor endurance; (4) Slow walking; and (5) Low physical activity. Participants who meet these criteria will nevertheless be classified as active if they reported a high amount of daily usual physical activity (climbing stairs or lifting weights). The outcome will be meeting one frailty criterion at least.

#### Physical activity

3.7.5

Physical activity will be assessed with a digital pedometer (Omron HJ-321 Tri-Axial) (30), to be placed front and middle on one thigh for a period of 8 consecutive days (30). In addition, the Global Physical Activity Questionnaire (GPAQ) will be used (31). This questionnaire is made up of 16 questions about PA carried out in a typical week, differentiating between the different types of activity in work, travel and free time. Data is collected on intensity (low/moderate/high), frequency (days / usual week) and duration (hours–minutes/typical day) of physical activities carried out in three domains: (1) work (paid employment or unpaid, study, housework or job search), (2) commuting (walking/cycling to get from one place to another), and (3) free time (leisure). A question is also included about sedentary behaviour (time usually spent sitting or lying down, excluding time spent sleeping at night).

#### Mobility

3.7.6

The Short Physical Performance Battery (SPPB) assesses three aspects of mobility: balance, gait speed and strength of limbs or lower limbs to get up from a chair (32).

#### Cognitive performance

3.7.7

The Montreal Cognitive Assessment (MOCA) (33) determines the existence of mild cognitive dysfunctions. It comprises 30 questions and takes 10–12 min to complete.

#### Primary outcome measures

3.7.8

The incidence rate of falls will be estimated based on the intervention and control group. Falls will be recorded using a daily log sent to the study centre monthly. On suffering a fall, participants must provide information about the time, date, injuries and prescribed treatment in relation to the fall, the fall location, and the movement which cause the fall. The person will be interviewed by telephone to correct any lack of data to determine the injuries details and to confirm their health status at this time (7).Quality of life will be measured through the EuroQol 5D questionnaire, validated in Spanish (34). This questionnaire comprises five items (mobility, personal care, daily activities, pain/discomfort, and anxiety/depression) and a self-assessed thermometer of health status.

#### Secondary outcome measures

3.7.9

Fear of falling: Short Falls International Scale of Efficacy (Short FES-I) assess “concerns about falling” (35). The scale is the falls efficacy scale-international short version, comprising seven items (items 2,4,6,7,9,15 and 16). Item responses are coded on a 4-point Likert scale: (1) not at all concerned, (2) somewhat concerned, (3) fairly concerned, and (4) very concerned.Exercise adherence will be measured using the Exercise Adherence Rating Scale (EARS) as part of the schedule sent in monthly. This scale is composed of 16 items, scored using a 5-point Likert scale (0 = completely agree to 4 = completely disagree) with a total summed score range from 0 to 64 (36).Cost-effectiveness of the intervention: Incremental cost-effectiveness ratio (ICER) related with the ratio of the difference in costs to the health effects difference in both interventions (37). These costs include outpatient treatment, formal/informal care, medication, transportation, room rental, intervention costs involving labour costs, staff and participants transportation, and materials.

### Procedures

3.8

Six months after the initial control group assessment and six months after the intervention group sessions have finished, subjects of both groups will be assessed with the same tests that were carried out in the initial assessment. After random assignment, follow-up assessments will be performed by the blind group assignment assessors. The database used in this study will only display information unrelated to the intervention when they are logged in to ensure the blinding of assessors. Should a participant wish to withdraw from the study, they will continue to be eligible to complete the follow-up measurements with their consent. Researchers will record the reasons and date of withdrawal, but data recorded before withdrawal will be used unless the participant decide to use their right to have all data deleted.

Study data will be collected and managed using REDCap electronic data capture tools, hosted at the University of “X.” REDCap is a secure, web-based software platform designed to support data capture for research studies.

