### Sample size

3.3

The main variable of the study was used to estimate the sample size, the annual incidence rate of falls in this population. An alpha risk of 0.05 and a beta risk of 0.2 (Power for Chi square 80% and t-test 94%), effect size estimated 0.30 (Cohen D) and 0.01 (V de Cramer) in a two-sided contrast has been accepted, 325 participants in the intervention group and 325 in the control are needed to find differences of ten percentage points as statistically significant between the control group, expected to be 30% [the estimate of falls in people older than 65 years of age (3, 5, 6)] and the intervention group, expected to be 20%. A give up rate of 10% during follow-up has been estimated.

This data has been calculated following the formula for qualitative variables published by Argimon Pallàs et al. (25).

$N=\frac{Za.Ö\;2.p.\left(1-p\right)+ZbÖ\;p1.\left(1-p1\right)+p2.\left(1-p2\right)2}{\left(p1-p2\right)2}$

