### Statistical analysis

3.9

The study population baseline characteristics will be expressed as means ± standard deviation (SD) for quantitative variables and in frequency distributions for categorical variables. Student’s t-test, chi-square, and Fisher’s exact tests will be applied to find differences in baseline characteristics between intervention and control groups. All analyses of the variables obtained from the questionnaires will be analyzed using the reliability and validity criteria proposed by their authors.

The main analyses will be performed on the intention-to-treat principle, so all randomised subjects will be included in the data analysis set for which the initial assessment was performed. Participants who withdraw or drop out will be asked to be included in follow-up measurements; those lost to follow up will be considered in the full set of analyses as missing data. Detailed modelling of variations between participants and groups will be done in terms of factors such as dose, acceptability, and contextual factors. Using the Chi-square test, we will compare the proportions of subjects who have had a fall in both groups. The comparison of all outcomes between baseline, six and twelve months will be carried out using the two-way repeated measures ANOVA. Logistic regression analysis will be conducted to determine the influence of the different risk factors on falls. Statistics analysed will be performed with SPSS V.25.0 statistical package (SPSS Inc., Chicago, Illinois, United States). *p* values for cut-off values for significance were established at <0.05 (two-tailed). Results were interpreted according *[Cohen]*, who considers small size if Cohen D are between 0.2 ≤ and < 0.5; average effect size if differences are between 0.5 ≤ and < 0.8 and very high effect size if differences are ≥0.8 (38).

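### Follow-up is timed from different starting points in the two arms and the fall-counting window is not fixed, so quality of life is compared at unequal times and the comparison of fallers may be biased against the intervention

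*Protocol article*

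**What the plan says.** Procedures (3.8) repeats the baseline tests in both arms "Six months after the initial control group assessment and six months after the intervention group sessions have finished". The first clock belongs to control and the second to intervention. Stage three (3.6.3) gives the programme length: "The total intervention comprises twelve weeks according to the following schedule". Its Table 1 puts the last on-site session in week 6 and the last telephone session in week 12. Participant assessment (3.4) places randomisation after the initial assessment, so baseline is close to time zero in both arms.

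Other sections describe follow-up differently:
- Sample size (3.3) is built on "the annual incidence rate of falls in this population".
- Stage four (3.6.4) names one evaluation, at six months.
- Statistical analysis (3.9) compares all outcomes at baseline, six and twelve months, without distinguishing the arms.

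Falls are collected by a daily log returned monthly (Primary outcome measures, 3.7.8). No start or end of counting is given there. The test is stated in 3.9: "Using the Chi-square test, we will compare the proportions of subjects who have had a fall in both groups".

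**The concern.** Two consequences follow from the arm-specific clock.

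**Visit-based outcomes.** EQ-5D (primary), Short FES-I and physical activity belong to the battery repeated at the 3.8 assessment. They are measured about 12 weeks later after randomisation in intervention than in control. The repeated-measures ANOVA in 3.9 nevertheless treats six months as one time point. Any change with time since randomisation is then mixed with the treatment effect.

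**Falls.** The proportion of people with at least one fall rises with time at risk, and the chi-square test has no exposure term. If falls are counted up to the 3.8 assessment, the intervention arm has longer to accumulate fallers. An effective programme could look ineffective, and an inert one could look harmful.

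**Working it through.** **Inputs from Sample size (3.3).** "An alpha risk of 0.05 and a beta risk of 0.2", "in a two-sided contrast has been accepted"; annual risk of falling 30% in control and 20% in intervention; 10% dropout; 325 per arm.

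**Step 1: the plan's own figure.** With p1 = 0.30, p2 = 0.20 and mean 0.25:

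n = [1.96·√(2·0.25·0.75) + 0.8416·√(0.30·0.70 + 0.20·0.80)]² / 0.10² = (1.2002 + 0.5119)² / 0.01 = 293.2, so 294 per arm.

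Dropout gives 294/0.90 = 327 or 294·1.10 = 324. The stated 325 is reproduced within rounding. It rests on annual risks. After 10% loss, 325·0.90 leaves about 292 per arm.

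**Step 2: assessment times.** Control: 6 months, about 26 weeks. Intervention: 12 + 26 = 38 weeks; or 6 + 26 = 32 weeks if the sessions are taken to end with the last on-site one.

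**Step 3: risk over a window.** Assume a constant hazard (not in the documents): p(w) = 1 − (1 − annual risk)^(w/52).
- Control, 26 weeks: 1 − 0.70^0.5 = 16.3%
- Intervention with planned benefit, 38 weeks: 1 − 0.80^0.731 = 15.0%
- Intervention with no effect, 38 weeks: 1 − 0.70^0.731 = 22.9%
- Intervention with planned benefit, 32 weeks: 1 − 0.80^0.615 = 12.8%
- Intervention with no effect, 32 weeks: 1 − 0.70^0.615 = 19.7%

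**Step 4: rejection probabilities.** Two-proportion test, 292 per arm, 26 versus 38 weeks.
- Planned benefit: difference 1.3 points, standard error 0.0301. P(significant for benefit) = 1 − Φ[(1.96·0.0301 − 0.0129)/0.0301] = 6.3%; adding 0.8% in the wrong direction gives 7.1%.
- No effect: difference 6.6 points against intervention, standard error 0.0329 under the null and 0.0328 under the alternative. P(significant for harm) = 1 − Φ[(1.96·0.0329 − 0.0661)/0.0328] = 52%, where 2.5% is intended.

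**Step 5: the readings side by side.** The last two columns give 292 and 325 per arm.

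| Fall window (control / intervention) | Planned effect | Power | False finding of harm if no effect |
|---|---|---|---|
| 26 / 38 weeks | 16.3% vs 15.0% | 7% / 7% | 52% / 56% |
| 26 / 32 weeks | 16.3% vs 12.8% | 22% / 24% | 18% / 20% |
| 26 / 26 weeks from randomisation | 16.3% vs 10.6% | 53% / 58% | 2.5% |
| 52 / 52 weeks from randomisation | 30.0% vs 20.0% | 80% / 84% | 2.5% |

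**Step 6: another fall model.** Replace the constant hazard by a geometric count with annual means 0.30/0.70 = 0.4286 and 0.20/0.80 = 0.25, and risk m/(1 + m) after scaling m to the window. At 26 versus 38 weeks the planned effect is 17.6% versus 15.4% (power 11% at 292 per arm). With no effect it is 17.6% versus about 24% (46% significant). The conclusion depends on the windows, not on the hazard model.

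**The case against.** The strongest objection is that 3.8 does not govern fall counting. It times a repeat of the baseline battery, whereas falls come from the log, and nothing ties the end of the log to that visit. The annual rate in 3.3 and the twelve-month comparison in 3.9 both point to a period that could be common to both arms. The primary outcome is also worded as an incidence rate, which could be analysed per person-time. All of this stands. It makes the fall bias conditional. It does not remove the problem, because no section defines twelve months as the fall window, 3.8 describes no twelve-month visit, and the test named for falls is a chi-square on proportions.

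A reader might go further and infer three things that the document does not support:
- **That no other follow-up period is given.** Sections 3.3, 3.6.4 and 3.9 give others; the fault is that they disagree.
- **That counting only the six months after the sessions breaks the stated intention-to-treat rule.** That rule concerns which participants are included, and none would be excluded. The windows would have equal length, so the length bias above would not arise. Falls in the first 12 weeks would still go uncounted in one arm only, which is a real weakness.
- **That waiting for a group to fill lengthens the gap further.** The document does not say so.

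The supplementary SPIRIT figure was not available and may show the intended schedule. It would not cure the wording of 3.8.

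**Conclusion.** The unequal timing of the follow-up assessment is explicit: about 26 versus 38 weeks after baseline, or 26 versus 32 on the less natural reading, since Table 1 also numbers the telephone contacts as sessions. For EQ-5D, Short FES-I and physical activity this is a defect as written. Its size cannot be computed from the document.

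For falls, it would be tempting to say that the comparison is biased against the intervention. The document supports only that it may be. If falls are counted to the 3.8 assessment, the planned 10-point difference shrinks to 1.3 points with power about 7%, and an inert programme would appear significantly harmful in about half of trials. On the week-6 reading, power is 22–24% and false findings of harm 18–20%. A common 12-month window has neither problem. These figures assume the plan's annual risks, a constant hazard, 26 weeks for six months, and 292 to 325 per arm. Because both primary outcomes are touched, and assessments made at the wrong time cannot be repaired afterwards, this needs correcting.

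**What to change.** Reconcile Sample size (3.3), Stage four (3.6.4), Procedures (3.8) and Statistical analysis (3.9) to one schedule:

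1. Replace the arm-specific timing in 3.8 by assessments at the same times after the randomisation date in both arms.
2. State that falls are counted from randomisation over the same length of time in both arms, and name that length. Twelve months matches the sample size (80–84% power). A common 26-week window would remove the bias but give only 53–58%, and would need 547 per arm before dropout for 80%.
3. If exposure still differs between participants, for example through withdrawal, analyse falls as a rate with person-time rather than by crude proportions.

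The cost is a protocol amendment, rescheduling of the intervention arm's assessment, and fall logs kept for twelve months. A twelve-month assessment, which 3.9 already presupposes, must also be written into 3.8. One downside is that the six-month assessment would fall about 26 − 12 = 14 weeks after the programme ends, rather than about 26. Trial status (3.10) describes people still being invited, so the change was feasible early in recruitment.

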### Statistical analysis

3.9

The study population baseline characteristics will be expressed as means ± standard deviation (SD) for quantitative variables and in frequency distributions for categorical variables. Student’s t-test, chi-square, and Fisher’s exact tests will be applied to find differences in baseline characteristics between intervention and control groups. All analyses of the variables obtained from the questionnaires will be analyzed using the reliability and validity criteria proposed by their authors.

The main analyses will be performed on the intention-to-treat principle, so all randomised subjects will be included in the data analysis set for which the initial assessment was performed. Participants who withdraw or drop out will be asked to be included in follow-up measurements; those lost to follow up will be considered in the full set of analyses as missing data. Detailed modelling of variations between participants and groups will be done in terms of factors such as dose, acceptability, and contextual factors. Using the Chi-square test, we will compare the proportions of subjects who have had a fall in both groups. The comparison of all outcomes between baseline, six and twelve months will be carried out using the two-way repeated measures ANOVA. Logistic regression analysis will be conducted to determine the influence of the different risk factors on falls. Statistics analysed will be performed with SPSS V.25.0 statistical package (SPSS Inc., Chicago, Illinois, United States). *p* values for cut-off values for significance were established at <0.05 (two-tailed). Results were interpreted according *[Cohen]*, who considers small size if Cohen D are between 0.2 ≤ and < 0.5; average effect size if differences are between 0.5 ≤ and < 0.8 and very high effect size if differences are ≥0.8 (38).

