**Methods:**

The study will comprise 650 participants with more than 65 years who live at home, observing established inclusion and exclusion criteria. Participants will be randomly assigned in two groups: group intervention (*n* = 325) and standard health advice (*n* = 325). The intervention group will follow the balance and strength activities described in the LiFE program manual. The group intervention will be carried out in groups of 12–14 and will consist of seven one-hour sessions over 12 weeks in health centres. Incidence of falls and quality of life will be assessed as primary outcome variables. Fear of falling and exercise adherence will be analysed as secondary outcome variables.

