## Introduction

1

Practitioners and researchers are focused on ageing and frailty, as demonstrated by different initiatives (1, 2). It has been shown that in the population older than 70 years, frailty represent a 5.5 times higher adjusted risk of mortality, a 2.5 times higher risk of new disability, and a 2.7 times higher risk of loss of mobility (3). To reduce frailty, action must be taken on its main risk factor, sedentary lifestyle (4), and the prevention of falls is thus of particular importance; falls are among the five main health problems related with disability in people older than 60 years (5).

Approximately 30% of people aged over 65% and 50% of those over 80 who live in the community have one fall once a year as a minimum (3, 5, 6). Similarly, about 30% of those who fall suffer a new fall in the same year and 10% suffer several falls (7). Falling is, therefore, a risk factor for further falls. Furthermore, Noureldin et al. found that 15% of hospitalised older adults people had a fall within 30 days of discharge (8).

Falls represent a major cause of disability in older adults and over 50% present sequelae (5, 6); half of those suffering a fracture from a fall do not fully recover their previous functional level. Older adults are admitted to hospital for injuries related to falls more frequently and they also present discharges and consecutive readmissions over the following three years (8, 9). Besides, between 32% and 80% of patients who survive hospitalisation after a hip fracture are left with a permanent disability (10), being a 95% of hip fracture cases a result of falls (11). In this regard, it has been observed that physical exercise approaches can reverse the functional disability caused by hospitalisation in older patients (12).

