The objectives will be to assess if a group intervention implementing the sLiFE program principles reduces fall rates compared to standard advice; to assess whether fall prevention is more efficient in the group intervention than standard individual recommendations; to measure the incidence rate of falls according to participants’ level of physical activity; to assess medium- and long-term adherence to the exercise program and to find out the participants’ fear of falling.

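### The primary falls outcome is a rate, but the only fall-specific between-group test is a chi-square on the proportion who fell, which ignores repeat falls and time at risk

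*Protocol article*

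**What the plan says.** The first objective, at the end of the Introduction, is "to assess if a group intervention implementing the sLiFE program principles reduces fall rates compared to standard advice". Section 3.7.8 defines the primary falls outcome: "The incidence rate of falls will be estimated based on the intervention and control group". Its source is a diary: "Falls will be recorded using a daily log sent to the study centre monthly". Each fall is to be reported with its date, so repeat falls and observed time are both available. Quality of life is the other primary outcome; this point concerns falls only.

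Section 3.9 gives the fall-specific comparison of the arms: "Using the Chi-square test, we will compare the proportions of subjects who have had a fall in both groups". It also assigns all outcomes at baseline, six and twelve months to a two-way repeated measures ANOVA, and plans a logistic regression of risk factors for falls. On incomplete follow-up it says "those lost to follow up will be considered in the full set of analyses as missing data", while section 3.8 keeps data gathered before withdrawal unless the participant asks for deletion.

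Section 3.3 sizes the trial on what it calls an annual incidence rate, but enters proportions: 30% in controls and 20% under the intervention.

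**The concern.** A fall rate is the number of falls divided by time observed. The proportion of fallers uses neither the count beyond the first fall nor the time. The outcome and objective are on one scale, and the fall-specific test is on the other.

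Two things are at stake. The first is information: the Introduction says that "about 30% of those who fall suffer a new fall in the same year and 10% suffer several falls", and every one of those further falls drops out of a fell/did-not-fall comparison. The second is exposure: a comparison of proportions is fair only if both arms are watched equally long. Section 3.8 casts doubt on that, and it leaves the diaries of people who leave early without a clear place in the test.

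**Working it through.** **1. The plan's own sample size.** Inputs from section 3.3: 30% and 20%, two-sided alpha 0.05, power 80%, 10% dropout.

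n = [1.960·√(2·0.25·0.75) + 0.842·√(0.3·0.7 + 0.2·0.8)]² / 0.10² = (1.200 + 0.512)² / 0.01 ≈ 293.2, so 294 per arm. Dividing by 0.9 gives 327; multiplying by 1.1 gives 324. The stated 325 is reproduced, so the trial is sized for a proportion. With 10% lost, 0.9·325 = 292.5; I use 292 per arm, where chi-square power is 80%.

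**2. Falls not used.** Of 292 controls, 30% is about 88 fallers. If 30% of these fall again, at least 26 of at least 88 + 26 = 114 falls (23%) do not enter the test.

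**3. A rate model on the same assumptions.** The document gives no dispersion k, so k is my assumption. In a negative binomial, P(no fall) = (1 + kμ)^(−1/k). With k = 1:
- 70% without a fall gives μ = 0.3/0.7 = 0.429 falls a year; 80% gives μ = 0.2/0.8 = 0.25. The rate ratio is 0.58.
- P(2 or more | 1 or more) = 0.429/1.429 = 30%, and P(3 or more | 1 or more) = 9%. This is close to the Introduction's 30% and 10%, which is why k = 1 is the central case.

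Var(log rate ratio) = (1/μ₀ + 1/μ₁ + 2k)/n.
- 30% against 20% over 12 months: (2.333 + 4 + 2)/292 = 0.0285, SE 0.169, |log 0.583| = 0.539, z = 3.19, power Φ(3.19 − 1.96) = 89%.
- Rate ratio 0.69 (the 31% reduction cited in the Introduction): μ₁ = 0.296, or 22.8% fallers. (2.333 + 3.382 + 2)/292 = 0.0264, SE 0.163, z = 0.371/0.163 = 2.28, power 63%. Chi-square on 30% against 22.8% has 50%.
- Six months, same annual rates: means 0.214 and 0.125 (17.6% and 11.1% fallers); (4.667 + 8 + 2)/292 = 0.0502, z = 2.41, power 67% against 61% for chi-square. At rate ratio 0.69 over six months: 41% against 36%.

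| Scenario, 292 per arm | Rate model, k = 1 | Chi-square, k = 1 | Rate model, k = 0 to 3 | Chi-square, k = 0 to 3 |
|---|---|---|---|---|
| 30% vs 20%, 12 months | 89% | 80% | 84% to 95% | 80% |
| Rate ratio 0.69, 12 months | 63% | 50% | 68% to 52% | 62% to 32% |
| 30% vs 20% a year, seen for 6 months | 67% | 61% | – | – |

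**4. Time at risk.** Section 3.8 places the visit six months after initial assessment for controls, and six months after the sessions end for the intervention arm. Section 3.6.3 gives the programme twelve weeks, 84/30.44 = 2.76 months. Read literally, that is 6.0 months against about 8.8. Suppose falls were counted up to that visit (an assumption) and the true rates were equal at 0.429 a year with k = 1. The expected means are 0.214 and 0.429·8.76/12 = 0.313, so 17.6% and 23.8% fallers. Chi-square would then reject, in the direction of harm, in about 45% of trials (52% to 39% for k = 0 to 2). A follow-up offset removes this artefact if the fall rate is constant over time.

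**The case against.** The strongest reply is that the mismatch is one of wording. Section 3.3 uses incidence rate for a quantity of 30% against 20%, and the abstract says only "Incidence of falls and quality of life will be assessed as primary outcome variables". If the authors mean the proportion who fall in a year, the chi-square tests exactly what the trial was sized for. This stands in part: test and sample size agree, and with equal follow-up a chi-square on fallers is valid. It does not remove the conflict, because the objective, section 3.7.8, the diary and the 31% reduction used as motivation all concern rates.

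Several stronger readings are tempting and not supported:
- That chi-square is the only comparison stated. Section 3.9 also names the ANOVA and the logistic regression. Neither helps: the ANOVA has no person-time term and suits sparse, skewed counts poorly, and the logistic model is again binary and aimed at risk factors.
- That the sample size is wrong. It reproduces.
- That people lost early will be counted as not having fallen. Section 3.9 calls them missing, and section 3.8 keeps their earlier data.
- That the trial will show spurious harm. Step 4 depends on where counting stops. Section 3.9 names six and twelve months, and dated logs can be cut at a common point.

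The power gain also depends on the assumed dispersion and on 12 months of observation; at six months it is about 5 to 6 points. The low power at a rate ratio of 0.69 mostly reflects an effect smaller than the design assumed, since the rate model reaches only 63% there.

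**Conclusion.** The point holds as a mismatch in the text: the primary falls outcome and first objective are rates, while the fall-specific test between arms is on a proportion, and no stated analysis yields a rate ratio. This is not a detail left to a plan that is not shown, because the article does name a test.

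The cost in power is moderate: about 9 points for the design effect over 12 months, 12 to 13 at a rate ratio of 0.69, and 5 to 6 over six months, all at dispersion 1. In the 12-month scenarios the rate model stays ahead for every dispersion from 0 to 3. The possible bias from unequal exposure is potentially more serious but conditional on how section 3.8 is applied.

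**What to change.** - In section 3.9, make the primary falls analysis a negative binomial regression of the fall count on arm with log(days of diary follow-up) as offset. Include everyone with any diary data and report the rate ratio with its 95% CI.
- Keep the proportion with at least one fall, over a fixed period equal in both arms, as the secondary analysis that matches the sample size.
- Use one definition of the falls outcome in the objectives and in sections 3.3, 3.7.8 and 3.9.
- Reconcile the six-month follow-up of sections 3.6.4 and 3.8, including its different starting points by arm, with the six and twelve months of section 3.9.

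The diary data are already to be collected, standard software fits the model, and section 3.10 shows recruitment only beginning. The one real cost is in section 3.3: it must say that the number rests on the proportion of fallers, or be restated on the rate scale. At dispersion 1 over 12 months, with (1.960 + 0.842)² = 7.85, the restated number before dropout would be 7.85·8.333/0.539² ≈ 226 per arm for 30% against 20%, or 7.85·7.715/0.371² ≈ 440 for a rate ratio of 0.69. The target effect would therefore have to be chosen explicitly.
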